**Figure 1. f1:**
[figure not shown]
Hypothesis 1: Completion of the CARA conditional caution leads to a reduction in incidence and/or severity of DVA at the population level.

**
*Data source*
**: Data held on the police Record Management System (RMS) database, or equivalent, will be extracted, pseudonymised and shared in aggregated form.

**
*Population*
**: The population sample to be included in the analysis are those that are eligible for the CARA intervention.

**
*Intervention*
**: Those who have undertaken the CARA intervention will form the intervention group. CARA is a conditional diversionary caution offered by the police to first time adult offenders of DVA of standard risk or medium risk (in some areas). Offenders are required to undertake two mandatory workshops that increase awareness of their abusive behaviour and the safety of partners and children. In contrast to restorative justice, CARA is an awareness raising intervention for offenders, that utilises a trauma informed approach and motivational interviewing techniques across the pair of workshops. In these workshops offenders are further signposted onto services that support improvements in the wider determinants of their offending behaviour, such as to their GP, drug and alcohol services or onto a community perpetrator programme.

**
*Comparison*
**: Using PSM approaches a comparator group will be formed from those who meet the eligibility criteria for CARA but are based in an area that is currently not delivering the CARA intervention. Covariates for the matching will include demographics, such as age, gender, ethnicity, whether in same sex relationship; offending behaviour/wider determinants, such as offending history and/or risk profile, mental health, employment status, alcohol misuse, accommodation type and; wider contextual factors, such engagement with other perpetrator interventions.

**
*Outcome measures*
**: The primary outcome will be DVA
reoffending within 12 months. The primary outcome will be described as either i) number of DVA arrests ii) number of DVA crimes. The secondary outcome(s) will include for example total number of arrests, crime severity score, total number of offences.

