### Analysis of quantitative data

**
*Interrupted time series*
**. Using interrupted time series (ITS), we will also examine whether the introduction of the CARA conditional caution leads to a hypothesised population-based reduction in the incidence of DVA, as hypothesised in Figure 2. A secondary outcome will be to assess if there was a change in the severity of recorded DVA before and after the introduction of CARA.

 As an intervention study design, ITS is a valuable study design compared to traditional observational study designs (such as cohort or case control studies) particularly when there is a need for retrospective evaluations which have already been implemented, either without randomization or to a whole population, both of which are applicable in the CARA intervention (
Bernal *et al.*, 2017). By nature, ITS can be applied to natural experiments when an intervention is introduced at the population level at a clearly defined period of time and involves observing a single population over time.

In an ITS study, a time series of the outcome of interest (incidence of domestic violence and abuse) is used to establish an underlying trend, which is ‘interrupted’ by an intervention (e.g. CARA being offered in a force area) at a known point in time. The pre-intervention underlying trend is compared with the post-intervention period to identify whether the intervention is associated with any changes in outcome.

Initially summary statistics and plots will be undertaken, including a scatter plot of the time series demonstrating before and after comparisons of the incidence of DVA across the force areas. These will include sub-analyses, by age, gender, ethnicity, force area and whether in same sex relationship.

Following this a segmented regression model such as the one below will be constructed to undertake the ITS model:

Yt-=α+β1Tt+β2Xt+β3XtTt

Yt is the aggregated outcome variable measured at each equally-spaced time point (month)

Tt is time

Xt is study phase

XtTt is time after interruption

α, β1, β2 and β3 are model parameters

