As our outcome measure (DVA occurrences) are count data, we will also undertake a Poisson model. Calendar quarters will be included as a categorical variable to account for seasonality. The final model will provide a measure of relative risk with 95% confidence intervals to describe the change in incidence in DVA across the CARA sites before and after the introduction of the intervention. We will account for covariates of interest in the final model to examine any changes specific to offender subgroups of interest, including age, sex, ethnicity and socioeconomic status. Confounding events or co-interventions that will affect study outcome will be explored through consultation with the research team, including all stakeholders, and through the qualitative research. Time varying confounders might include, for example, lockdowns from the COVID-19 pandemic.

Where possible we will also aim to undertake a controlled interrupted time series (CITS) (
Bernal *et al.*, 2018). In this case the control data will be derived from sites where CARA was not delivered during the study timeframe. The CITS model can be described as:

Yt-=α+β1Tt+β2Xt+β3XtTt+β4Zt+β5ZtTt+β6ZtXt+β7ZtXtTt

Yt is the aggregated outcome variable measured at each equally-spaced time point (month)

Tt is time

Xt is study phase

XtTt is time after interruption

Zt is treatment or control group

ZtTt is time for treatment and 0 for control,

ZtXt is study phase for treatment and 0 for control,

ZtXtTt is time after interruption for treatment and 0 for control

α, β1, β2 , β3 β4, β5, β6 and β7 are model parameters

**
*Geomapping*
**. We will also undertake geomapping using postcode data from regional and national data (either from the address where the incident took place or the perpetrator’s address). The postcode data will be input using googlemaps to generate a visual-coloured map. The visuals produced through this method are not accurate enough to render an individual’s home address to become identifiable; postcodes are replaced with colour patches, similar to heat maps, covering a large area. The postcodes entered into google through this process are not stored by google and therefore no data will be stored and shared through this method.

**
*Health economics analysis*

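### The population-level relative risk rests on a single-group before-after model with no stated term for the lockdowns the plan names, while the controlled model it already writes out is left conditional

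*Protocol article*

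**What the plan says.** All of this is in the protocol article, mostly under Analysis of quantitative data (Interrupted time series).

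- **Design.** ITS is described as a design that "involves observing a single population over time".
- **Model.** "Following this a segmented regression model such as the one below will be constructed to undertake the ITS model". The equation has linear time, study phase and time after the interruption. For the Poisson version, "Calendar quarters will be included as a categorical variable to account for seasonality".
- **Reported result.** The final model gives a relative risk with a 95% confidence interval "to describe the change in incidence in DVA across the CARA sites before and after the introduction of the intervention".
- **Covariates.** "We will account for covariates of interest in the final model to examine any changes specific to offender subgroups of interest": age, sex, ethnicity and socioeconomic status.
- **Confounding events.** These are to be explored by consulting the team and stakeholders and through the qualitative work. "Time varying confounders might include, for example, lockdowns from the COVID-19 pandemic".
- **Controlled model.** "Where possible we will also aim to undertake a controlled interrupted time series (CITS"), with control data from sites that did not deliver CARA during the study timeframe. The equation is written out in full, including the group-by-phase (β6) and group-by-slope (β7) terms.
- **Other non-CARA data.** Under Population, intervention, comparison and outcome, the matched comparator consists of people who "are based in an area that is currently not delivering the CARA intervention". No feasibility condition is attached.

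Strengths and limitations describes the population analysis as ITS and does not mention a control series.

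**The concern.** The plan identifies a threat to the population analysis but states no means of removing it in the model that produces the reported relative risk. Quarter terms absorb a seasonal pattern that recurs every year, not a one-off event. The subgroup covariates describe offenders, not calendar time. Consultation can identify events, but the protocol does not say that what it finds will enter the model. The controlled model, which would remove changes shared with other forces, is an optional addition.

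If recorded DVA moved nationally close to a force's start date, through a lockdown, a recording change or a reporting trend, the single-group model would report that movement as an effect of CARA. It could show a reduction that did not occur or hide one that did. Change in incidence at population level is a stated objective, and the dissemination plan takes the results to the Home Office and the Ministry of Justice.

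**Working it through.** **Inputs.** The protocol gives the model form, monthly time points, the Poisson model and the quarter terms. It gives no series length, monthly count, start date, shock size, power or error rate for the time series. There is therefore no stated figure to reproduce, and everything below is illustration.

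**Assumed:** 24 months before and 24 after the start, 2,000 records a month, no CARA effect, and a national shift of 10%.

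**Model fitted:** log E(Yt) = α + β1·T + β2·X + β3·(time after start)·X + quarter terms, fitted to noise-free expected counts. Level RR = exp(β2). RR at 12 months = exp(β2 + 12·β3). The true value of each is 1.00.

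| Shared 10% shift | Level RR with quarter terms | Level RR without |
|---|---|---|
| Rise in the 3 months before the start | 0.963 (0.932 at 12 months) | 0.955 (0.924 at 12 months) |
| Rise in the first 6 months after the start | 1.07 | 1.08 |
| Lasting change from the start | 1.10 | 1.10 |
| 3-month rise far from the start (months 7-9 or 35-37) | about 1.00 to 1.02 across these fits | |

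The Poisson SE of the log level RR is 0.014 with quarter terms and 0.013 without. The quarter-term column is the one that matches the protocol.

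**Bias against precision (quarter terms in):**
- ln(0.963) = -0.038, and 0.038 / 0.014 = 2.7 SE. The interval is exp(-0.038 ± 1.96 × 0.014), about 0.94 to 0.99, which excludes 1.
- ln(1.07) = 0.068, and 0.068 / 0.014 = 4.8 SE.
- ln(1.10) = 0.095, and 0.095 / 0.014 = 6.8 SE.

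**Lockdown indicator.** A correctly dated indicator in the single-group model returns a level RR of 1.00 for the temporary shocks. It cannot repair a lasting change that begins with CARA, because the indicator would coincide with the phase term. Only a control series can separate those two.

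**Controlled model.** With a control series 0.6 times as large and the same relative shift, exp(β6) and exp(β7) are both 1.00 in every scenario. The SE of β6 is about 0.021. This agrees with 0.013 × √(1 + 1/0.6) = 0.013 × 1.63 = 0.021.

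**Second set of assumptions.** Take 72 months, about 500 counts a month, a 13-month shock of RR 0.9, 1.1 or 1.2 in months 38-50, quarter terms included, and CARA starting at month 24, 36, 38, 44 or 51. The single-group step RR then runs from 0.85 to 1.23. The controlled step is 1.00 if control sites have the same shock. It is 0.92 to 1.11 if they have half the log shock, so the bias is roughly halved but not removed.

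**The case against.** **The remedy is largely in the plan already.** The protocol names the controlled model, states its control source and writes out all eight parameters. Nowhere does it label the single-group model main or primary, and it offers the equation as an example. This stands as to labels. The ranking has to be inferred from the final-model sentence, the conditional wording of the controlled analysis and the Strengths and limitations section, but all three point the same way.

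**A reader might infer that an uncontrolled series can never remove a lockdown effect.** The documents do not support that. A dated indicator removes a temporary shock, and a fuller plan might list such terms. The point is limited to the model as written, which states none, and to lasting changes, which an indicator cannot remove.

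**A reader might also infer that control series are assured because the matched cohort uses non-CARA areas.** That does not follow. The Introduction says CARA has been rolled out nationally, the Abstract promises data from up to nine forces, and the nine forces named under Sampling and recruitment strategy all deliver CARA. Sharing agreements are signed by most areas, not all. The matched cohort needs areas not delivering CARA at present, whereas the controlled series needs sites without it throughout the study timeframe, with monthly counts. Some condition on feasibility is therefore reasonable.

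**The figures depend on where the shock falls.** This stands. Shocks far from the start give level RRs of about 1.00 to 1.02. In an assumed case with nine starts six months apart over 96 months, force-specific RRs ran from 0.976 to 1.019 and averaged 0.998. Staggered starts could therefore dilute a temporary shock considerably, but the protocol gives no start dates and does not say how they enter the model.

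**Conclusion.** The concern holds in a limited form. As written, the population-level relative risk is a single-group before-after contrast. It attributes to CARA a shared national change near a force's start date, and the controlled model that would address this is optional. Under the 24+24-month assumptions with quarter terms, the false RR is about 0.96 for level and 0.93 at 12 months, 1.07, or 1.10, according to the timing of the shift, against an SE of 0.014. These figures show direction and order of size only. They assume a 10% shift, 2,000 records a month, a single start date and pure Poisson variation.

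This should be fixed, but it is not a fatal flaw. A reader might infer that the study's main result is compromised. It is not: the stated primary outcome, DVA reoffending within 12 months, uses a matched cohort with comparators from non-CARA areas. That cohort addresses individual reoffending, however, so it does not answer the population question in place of a controlled series.

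**What to change.** 1. State that the controlled model carries the population conclusion wherever monthly counts can be obtained from forces without CARA during the study timeframe. Ask the non-CARA areas used for the matched cohort first.
2. Read the CARA effect from β6 and β7, using each force's own start date.
3. Keep the single-group ITS as supportive.
4. In both models, include lockdown-period indicators whose dates are fixed before outcome data are seen.
5. If no control series can be obtained, report the single-group result, with those indicators, as not separable from concurrent national changes.

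**Cost.** The change needs a revision to the analysis text and a request for monthly counts from control forces. Precision falls: in the illustration the SE is about 0.021 against 0.013 (without quarter terms, controls 0.6 times as large). The controlled model removes only shocks that the control forces share.

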## Ethics and governance

Research ethical approval has been sought from the University of Southampton (Higher Education Institute) Ethical Committee and approved on the on the 1
^st^ June 2022 (Ref: ERGO ID: 71818.A1) As this research study is not being conducted within prisons nor within the national health service, neither HM Prison and Probation Service or Health Research Authority approval will be needed, respectively. Upholding ethics, good governance and quality in practice is central to all processes. The project will also comply fully with the ESRC's Research Ethics Framework, The Offender Health Research Network and GDPR. This includes upholding the ethical research governance in line with the Ethics Policy Statement at the University of Southampton
https://www.southampton.ac.uk/about/governance/policies/ethics.page.

There are a number of central tenets that should be maintained throughout the research. These include the moral principles guided by four main principles of bioethics (
Beauchamp & Childress, 2013). The principles are autonomy (informed consent), non-maleficence (do no harm), positive beneficence (benefits of research outweigh the risks) and justice (research strategies and procedures are just and fair).

Police data will be shared as anonymised, aggregated form. Information sharing agreements have been developed and have been signed by the majority of force areas. No additional permissions are required to access this routine data. The lead researcher handling police data will undertake national police vetting with Warwickshire police in order to handle police data. Each police force will be required to develop, regularly review and sign a Data Protection Impact Assessment (DPIA) for the project.

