**. The aim of the health economic analysis will be to examine the cost-benefits of Project CARA with matched controls. Relevant benefits will include incidents of reoffending and quality adjusted life years (QALYs) obtained from the published literature. Cost considerations will include the cost of delivering Project CARA, including mobilisation and ongoing delivery costs and for both groups we will examine lost economic output, health, legal, social and specialist resources and any personal resource consequences (for example damages, divorce). The perspective of the analysis will include health and social care, criminal and legal and specialist services in the first instance and will explore the inclusion of costs to the victim in a wider cost perspective.

Data sources will include the CARA victim contact form, Crime Survey for England and Wales, and information collected from police taking part in the project. Unit costs will be taken from relevant sources such as the Home Office or Department of Health and Social Care. Results will be presented in a cost-benefit analysis as incremental costs per reoffence avoided and incremental costs per QALY. Probabilistic sensitivity analysis (PSA) will be used to allow for uncertainty around cost and effectiveness estimates.
*
**
**
*

**
*Routine service data*
**. Routine data from the main third sector implementing agencies will be used to examine the fidelity, dose and reach of the CARA intervention. Routine data sources may include, for example, video observations of group work, referral forms and outcome questionnaires. These will be summarised descriptively. All quantitative data sources will be aggregated.

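### Geomapping enters incident or perpetrator postcodes into an outside online map service, which sits badly with the aggregated-data rules and is not made safe by the statement that the service does not store them

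*Protocol article*

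**What the plan says.** Four places in the protocol article bear on this.

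- *Ethics and governance*: "Police data will be shared as anonymised, aggregated form". The same section describes information sharing agreements, police vetting of the lead researcher who handles police data, and a requirement that each force regularly review and "sign a Data Protection Impact Assessment (DPIA) for the project".
- *Population, intervention, comparison and outcome* (Data source): records from the police management system will be "extracted, pseudonymised and shared in aggregated form".
- *Analysis of quantitative data* (Geomapping): "We will also undertake geomapping using postcode data from regional and national data". The location is taken "either from the address where the incident took place" or from the perpetrator's address. Then: "The postcode data will be input using googlemaps to generate a visual-coloured map". Two safeguards follow. The picture shows broad patches of colour, too coarse to reveal a home. And "The postcodes entered into google through this process are not stored by google", from which the article concludes that the method neither stores nor shares any data.
- *Analysis of quantitative data* (Routine service data, closing sentence): "All quantitative data sources will be aggregated".

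**The concern.** There are two linked problems in what is written, and a smaller one about how the map will be read.

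First, a postcode taken from an incident or perpetrator address derives from an individual record. The article sets an aggregation rule for its data, then describes a step whose input is postcodes, without saying how they reach the team in aggregated form.

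Second, the reassurance about the outside service is a faulty inference. Storage by the recipient and disclosure to the recipient are different things. Even if the service keeps nothing, the postcodes have been sent to it. In domestic abuse data the incident address may be the victim's home, so this is a sensitive item on which to rest a safeguard that does not hold. A force's impact assessment that relied on this sentence would rest on a wrong premise.

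Third, the article does not say whether the colour represents counts or rates, or which of the two addresses is used. Where abuse happens and where offenders live are different questions. The quantitative study's population-level aim concerns incidence, so readers may take the map as showing incidence whether or not it does.

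**Working it through.** The article gives no figure for geomapping, so there is nothing to reproduce. The check compares the statements and adds one illustration on assumed values.

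**Step 1: the data rules.** *Ethics and governance* says anonymised and aggregated. The Data source paragraph says pseudonymised and aggregated. These are not the same: pseudonymised records can be linked back by whoever holds the key, anonymised records cannot. The closing sentence under Routine service data extends aggregation to all quantitative sources.

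**Step 2: the geomapping input.** It is postcodes tied to an incident or perpetrator address. Nothing in the paragraph says they are grouped before entry. If they are entered one per record, the step conflicts with the aggregation rule. If they are counts per postcode, the data are technically aggregated, but cells could be very small and the article states no minimum. On either reading some explanation is needed.

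**Step 3: what each safeguard covers.**

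| Safeguard | Input to the service | Finished map |
|---|---|---|
| Broad colour patches | Not covered | Covered |
| Service does not store postcodes (asserted) | Covers retention, not transmission | Not relevant |
| Agreements, impact assessments, vetting | Transfer to a map service not mentioned | Not mentioned |

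No safeguard described in the article addresses the sending of postcodes to an outside party.

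**Step 4: counts against rates (illustration).** Assume two areas of 5,000 and 50,000 residents with the same underlying rate. The count is the rate times the population.

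| Assumed rate per 1,000 | Count, 5,000 residents | Count, 50,000 residents | Count ratio | Rate ratio |
|---|---|---|---|---|
| 5 | 5 × 5 = 25 | 5 × 50 = 250 | 10 | 1.0 |
| 10 | 10 × 5 = 50 | 10 × 50 = 500 | 10 | 1.0 |
| 20 | 20 × 5 = 100 | 20 × 50 = 1,000 | 10 | 1.0 |

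The contrast equals the population ratio whatever the rate. It arises only if undivided counts are coloured, which the article neither states nor excludes.

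**The case against.** The strongest reply is that the article shows a tension rather than a breach. The rule in *Ethics and governance* covers police data, whereas the geomapping paragraph names its source only as regional and national data, which need not all come from the police. Counts per postcode would be a form of aggregation. Agreements, per-force impact assessments, vetting and ethics approval are in place. Areal units, denominators and suppression rules are details that a journal article may leave to the full protocol or analysis plan. Geomapping also feeds none of the matched cohort, time-series or cost analyses.

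Much of this stands. It rules out several stronger readings that a reader might infer:

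- *The map will display raw locations.* The article says the opposite: postcodes become patches covering a large area.
- *The map shows where people live instead of where abuse is frequent.* This would need undivided counts to be coloured, which is not stated. The incident address is one of the two options, and the article never says that the map estimates incidence.
- *The two address types will be pooled or treated as equivalent.* An either/or wording leaves the choice open and shows no pooling.
- *The article flatly contradicts itself on data sharing.* Unidentified sources and possible grouping by postcode leave room for a consistent reading, though the article does not supply one.

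The reply does not remove the core. Unidentified sources do not escape the sentence on all quantitative data. That sentence does close the paragraph on routine service data and could be read more narrowly, but its wording is general. The governance described does not mention transfer to a map service. The inference from non-storage to non-sharing is an error in the text itself, which no unseen document can excuse.

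**Conclusion.** The point holds in a limited form. The inference that no data are shared because none are stored is wrong as written. The postcode input is hard to reconcile with the three data statements, which also differ between anonymised and pseudonymised.

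The size of the disclosure risk cannot be worked out from the document, and whether the service stores postcodes cannot be checked from it. The tenfold contrast rests on assumed populations and on counts being coloured; it is a reason to specify rates, not evidence that the planned map is misleading. Because geomapping is descriptive, the main effect estimates are unaffected. The change is worth making because the data are sensitive and the remedy is cheap.

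**What to change.** 1. Reconcile *Ethics and governance*, the Data source paragraph, the Geomapping paragraph and the closing sentence under Routine service data. State one rule on anonymised or pseudonymised data, and say in what form location data reach the team.
2. Delete the inference that non-storage by the service means that nothing is shared.
3. Have the forces, or the vetted analyst, convert postcodes to small-area codes before release. Produce the maps in offline software with small counts suppressed.
4. Map rates per resident of each area rather than counts. If both incident-address and perpetrator-address maps are made, keep them separate and label each.

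The cost is coarser maps and slightly more work: an area look-up, area population figures and an offline mapping tool. No other analysis needs to change.
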